## Abstract

**Background:**

Rheumatoid arthritis (RA) is a chronic autoimmune disease characterized by swelling and painful joints, eventually leading to joint destruction. There is still a lack of effective therapy to treat RA. The Juanbi pill is a Chinese medicine that has been widely used to treat active RA in China for hundreds of years, relieving pain and protecting the affected joints from malformation. However, there is no solid evidence to show the effect of the Juanbi pill on the management of active RA.

**Methods/design:**

We will conduct a multicenter, randomized, double-blind, placebo-controlled clinical trial to determine whether the traditional Chinese medicine Juanbi pill could relieve joint pain in RA and protect the joints. A total of 120 patients with active RA will be enrolled and treated with the Juanbi pill or a placebo for 3 months. The primary outcome measures are as follows: rate of in the American College of Rheumatology (ACR)50, change in the 28-joint Disease Activity Score (DAS28) from baseline at beginning of therapy to 3 months, and a change in the van der Heijde modified Sharp score measured from baseline to 12 months. The secondary outcome measures are as follows: rate of change in ACR20, ACR70, Health Assessment Questionnaire-Disability Index (HAQ-DI), and change in score in the Patient Assessment of Arthritis Pain, Patient Global Assessment of Arthritis, and the Athens Insomnia Scale (AIS) from baseline to 2-week, 1-month, 2-month, 3-month, 6-month, and 12-month follow up. In addition, the rate of change (score) in the ACR50 and DAS28 from the baseline to 2-week, 1-month, 2-month, 6-month, and 12-month follow up are also the secondary outcome measures.

**Discussion:**

Although the Juanbi pill has been used in China for many years to treat RA, there is a lack of consensus about its effectiveness. This trial will provide convincing evidence about the effect of Juanbi pill on active RA.

**Trial registration:**

ClinicalTrials.gov, NCT02885597. Registered on 30 August 2016.

**Electronic supplementary material:**

The online version of this article (10.1186/s13063-018-2555-1) contains supplementary material, which is available to authorized users.

## Background

Rheumatoid arthritis (RA) is a chronic autoimmune disease that is characterized by pain, swelling, synovial inflammation, joint damage, and bone destruction, resulting in severe disability and increased mortality rate [1]. The prevalence of RA worldwide is estimated to be 0.5–1%, with a mean annual incidence of 0.05% [2, 3]. Much research has been done to find an approach to alleviate the swelling and tenderness of joints and avoid irreversible joint impairment. Nevertheless, the treatment approaches for RA are still limited [4].

Herbal medicines, which are complementary and alternative medicines (CAM), have been used for centuries in China to treat different illnesses [5, 6]. In traditional Chinese medicine (TCM), RA is known as *Bi syndrome*, and *Juan Bi* (means getting rid of *Bi syndrome* in Chinese) decoction from the book *Yi Xue Xin Wu* from the Qing Dynasty was specially designed to treat *Bi syndrome* [7]. The Juanbi decoction is composed of Radix angelicae pubescentis, Notopterygium incisum, *Cinnamomum cassia* Presl, Gentiana macrophylla Pall., Angelica sinensis (Oliv.) Diels, Ligusticum chuanxiong Hort., Glycyrrhiza uralensis Fisch., Caulis Piperis Kadsurae, *Morus alba* L, Olibanum, and Radix Aucklandiae, and has been widely used to treat arthritis in China [8–10]. Our preliminary screening identified that Juanbi decoction attenuates inflammation of the ankle joints in TNF-transgenic (TNF-Tg) mice, a chronic inflammatory arthritis mouse model (data not shown).

Juanbi decoction combined with methotrexate (MTX) has been widely used in China for treatment of RA, and case report studies show that Juanbi decoction can help MTX attenuate joint pain and swelling [11–13]. However, there are few data from large-scale randomized trials on the efficacy of Juanbi for the treatment of RA and its adverse effects. Therefore, we aimed to conduct a randomized, double-blinded, placebo-controlled trial to estimate the effectiveness and safety of Juanbi decoction for RA. The results of this trial will provide evidence on the value of the Juanbi decoction as an intervention to lower disease activity in RA and protect the affected joints from deformity. Considering the difficulty in assessing the quality of a decoction, we instead plan to use the Juanbi pill in our trial. The Juanbi pill is the raw extraction of Juanbi decoction used for convenience of quality control and long-term storage, and it has been used in our hospital for decades.

## Methods/design

### Study design

This study is a multicenter, randomized, double-blinded, placebo-controlled clinical trial with two parallel arms (Fig. 1). The aim of the study is to evaluate whether the Juanbi pill combined with MTX is effective for the management of active RA. In total, 120 patients with active RA will be recruited (60 patients per arm) from centers in Shanghai, China, from Longhua Hospital affiliated with Shanghai university of Traditional Chinese Medicine, Yueyang Integrated Medicine Hospital affiliated with Shanghai University of Traditional Chinese Medicine, and Shanghai Guanghua Hospital of Integrated Traditional Chinese and Western Medicine. The Standard Protocol Items: Recommendation for Interventional Trials (SPIRIT) 2013 checklist is shown in Additional file 1.

**Fig. 1 Fig1:**
[figure not shown]
Project overview. RA, rheumatoid arthritis; MTX, methotrexate

### Study participants

Participants will be recruited from three hospitals (Longhua Hospital, Shanghai Yueyang Integrated Medicine Hospital, and Shanghai Guanghua Hospital of Integrated Traditional Chinese and Western Medicine) by poster and hospital official website advertisements. The planned recruitment period is 12 months. Informed consent will be obtained from all participants before randomization.

### Eligibility criteria

#### Inclusion criteria

Participants who fulfill the following criteria are eligible:Adults (aged ≥ 18 y) with RASatisfy American College of Rheumatology (ACR)/European League Against Rheumatism (EULAR) criteria for RA, 2010 [4]Onset of symptoms within 12 months before enrollmentActive disease at the time of enrollment as indicated by 28-joint Disease Activity Score (DAS28) greater than 3.2 [14], and no prior exposure to oral glucocorticoids at a daily dose greater than 10 mg or to any biologic agentsPaid or unpaid employment but measurable work (e.g., caring for a family and home)

#### Exclusion criteria

The exclusion criteria are as follows:RA combined with other autoimmune disease, such as adjuvant arthritis, lupus arthritis, or osteoarthritisRA combined with abnormal liver and kidney functionWomen who are pregnant, planning pregnancy, or breast-feedingSevere chronic or acute disease interfering with attendance for therapyAlcohol or substance abuseUnable to understand or sign an informed consent form

### Interventions

All patients will be randomized into the Juanbi group or the placebo group. Patients in the Juanbi group will receive both the Juanbi pill (4 g/bag, two bags per day) and MTX (5 mg per week) for 3 months, whereas patients in the other group will receive a Juanbi pill placebo (4 g/bag, two bags per day) and the same dose of MTX as the Juanbi group. The Juanbi pill and the placebo are to be dissolved in 200 mL of hot water and taken orally twice a day for 3 months. The Juanbi pill will be manufactured, packaged, and labeled by Jiangyin Tianjiang Pharmaceutical Co., Ltd., based on good manufacturing practice standard. The crude herbs, including Rhizoma Et Radix Notopterygii (Qiang Huo) 18 kg, Radix Angelicae Pubescentis (Du Huo) 18 kg, Radix Gentianae Macrophyllae (Qin Jiao) 18 kg, Caulis Piperis Kadsurae (Hai Feng Teng) 36 kg, Ramulus Mori (Sang Zhi) 54 kg, Radix Angelicae Sinensis (Dang Gui) 54 kg, Rhizoma Chuanxiong (Chuan Xiong) 12.6 kg, Olibanum (Ru Xiang) 25.2 kg, Radix Aucklandiae (Mu Xiang) 25.2 kg, Radix Glycyrrhizae (Gan Cao) 9 kg, and Ramulus Cinnamomi (Gui Zhi) 9 kg, were supplied in one batch from Haozhou Hongyu Chinese Herbal Medicine Co., Ltd. or Anhui Huizhongzhou Chinese Herbal Medicine Co., Ltd. The test results of all herbs meet the standard. All herbs were stored in a specialized cool and dry place. The Juanbi pill is made as follows: (1) extraction: all herbs listed are put in a ceramic container and 1000 L of distilled water is added to macerate the herbs for 1 h. Then, the mixture is boiled at 100 °C for 1 h for the first extraction, and repeated twice to obtain three extractions in total. Note that the third extraction should contain only 500 L of distilled water and have only 30 min boiling time; (2) concentration: the three extractions are mixed and the mixture is concentrated at 60 °C (660 mmHg). The mixture is sprayed dry to produce an extract powder, which is smashed and screened through mesh size 80. The pills are packed in quantities of 4 g per bag and stored in a clean room at approximately 20 °C and 50% humidity. The Juanbi pill placebo contains 10% Juanbi pill and 90% bitterant, lactose edible essence, pigment (e.g., lemon yellow, caramel pigment, or sunset yellow), and starch, and has a similar shape, smell, color, and taste to the actual Juanbi pill. The Juanbi pill and the placebo all met the quality inspection standards.

The duration of the intervention is 3 months, and follow up is 9 months. Study visits will take place at baseline and at 2, 4, 8, 12, 24, and 52 weeks. Every patient will be asked to visit within 3 days of the given time point.

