### Sample size calculation

We calculated the sample size according to our primary study. We conducted a preliminary experiment from December 2015 to May 2016 into the efficacy of the Juanbi pill combined with MTX versus MTX alone, and we found that patients taking the Juanbi pill combined with MTX achieved 84.8% ACR50, whereas patients in the MTX group achieved 55.5% ACR50 response. According to the formula of the rate in completely random design:$$ \mathrm{n}1=\mathrm{n}2=\frac{\left[{u}_{\alpha /2}\sqrt{2\overline{p}\left(1-\overline{p}\right)}+{u}_{\beta}\sqrt{p_1\left(1-{p}_1\right)+{p}_2\left(1-{p}_2\right)}\right]\ }{{\left({p}_1-{p}_2\right)}^2}, $$

where n_1_ and n_2_ are the number of participants in the Juanbi and placebo groups, respectively, and *u*_*α*/2_=1.96 when type 1 error is 0.05, *u*_*β*_ = 1.282 when type II error is 0.1 in two-sided tests: $$ \overline{p} $$ is the mean of *p*_1_ and *p*_2_ [31]. It was estimated that approximately 50 participants per group were needed to achieve 90% power and a (two-sided) 5% significance level in detecting treatment differences. Thus, the final sample size has been set at a total of 120 patients (60 in each group), considering a 20% dropout rate. Forty participants (20 in the treatment group and 20 in the placebo group) from the three centers will be recruited.

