## Discussion

Chinese herbs have been widely used worldwide as CAM. A recent survey conducted in San Francisco showed that patients frequently used Chinese herbal products in conjunction with Western prescription medicines, which would be documented in the medical record [26]. Although many who people use Chinese herbs consider these treatments effective, there remains a need for a solid evidence to show the effectiveness and safety [27, 28].

Before we conducted this trial, we closely searched PubMed, EMBASE, the Cochrane Library, CINAHL, ISI web of knowledge, CNKI (including China Doctor/Master Dissertation Full Text Database and China Proceedings Conference Full Text Database), Vip Journal Integration Platform (VJIP), Wan Fang Data, Chinese BioMedical (CBM) databases (Sinomed), and clinical trials from the inception to December 2015, and we found no definite evidence about the effectiveness and safety of the Juanbi pill in the treatment of active RA. Therefore, we decided to conduct a multicenter, randomized, controlled clinical trial to closely study the effectiveness and safety. We will use the ACR50, DAS28, and van der Heijde modified Sharp score to estimate disease activity and damage in the affected joints; moreover, we will calculate the patients’ life quality using scales such as the HAQ-DI, AIS, and SF-36 as secondary outcome measures. We will assess the safety of the Juanbi pill in two categories: patients’ self-reporting of quality of life and symptoms, and laboratory examinations such as blood, urine, feces, and kidney and liver function tests, to obtain a full assessment. Due to lack of evidence about the effectiveness of the Juanbi pill, we will apply the pill combined with MTX to treat RA to ensure the compliance of participants and meet ethical considerations, since MTX is a first-line treatment among disease-modifying anti-rheumatic drugs, and can achieve 53.8% DAS28 remission [10, 30].

To the best of our knowledge, this is the first well-designed, randomized, controlled trial investigating the efficacy of the Juanbi pill combined with MTX for the treatment of active RA. This study is built on our preliminary open experiment with a small sample, as well as hundreds of years’ use of the Juanbi pill in China for the treatment of RA.

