This study is designed to answer whether the Juanbi pill combined with MTX is preferred in the treatment of active RA, compared with MTX alone. If this trial succeeds, it will provide the patients and physicians an option of combining the Juanbi pill with MTX to obtain better disease remission. Moreover, this trial will provide data about the effect of the Juanbi pill on joint pain and function, quality of life, and safety. The results will aid clinical decision-making for the management of active RA and will provide useful information that can be incorporated into future guidelines.

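### The placebo is 10% Juanbi pill, so the trial does not estimate the stated contrast with MTX alone, and its 90% power is justified only for an MTX-alone control

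*Protocol article*

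**What the plan says.** The protocol article describes the control product under Interventions: "The Juanbi pill placebo contains 10% Juanbi pill and 90% bitterant", the remainder also including lactose essence, pigment and starch. On how it is given: "patients in the other group will receive a Juanbi pill placebo (4 g/bag, two bags per day) and the same dose of MTX as the" treated arm. Both products are taken for 3 months.

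The Discussion says the study is designed to answer "whether the Juanbi pill combined with MTX is preferred in the treatment of active RA, compared with MTX alone".

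The Sample size calculation draws its rates from a preliminary experiment on "the efficacy of the Juanbi pill combined with MTX versus MTX alone". In it, "patients taking the Juanbi pill combined with MTX achieved 84.8% ACR50", whereas "patients in the MTX group achieved 55.5% ACR50 response". From these rates it concludes that "approximately 50 participants per group were needed to achieve 90% power and a (two-sided) 5% significance level". The Discussion adds: "This study is built on our preliminary open experiment with a small sample".

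No section says that the 10% content is inactive, allows for it in the sample size, or limits the conclusion to full versus one-tenth content.

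**The concern.** No arm in this trial receives MTX alone. Three descriptions of the control do not agree: the product given contains some of the test product, the stated question assumes none, and the planning rate comes from patients who took none and knew it.

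Three things are at stake.

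- **Interpretation of efficacy.** If the 10% content has any effect on ACR50, the observed difference is smaller than the difference from MTX alone. A null result could then mean either no effect or a narrowed contrast.
- **Justification of power.** The 55.5% control rate was seen under a different condition. It differs from the planned control in exposure to the product and in blinding, and either could make the actual control rate higher.
- **Safety.** Controls are exposed to the same herbs. If the 10% content itself causes events, between-arm differences would mask part of the risk.

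**Working it through.** **Inputs from the protocol article.** Juanbi plus MTX ACR50 rate p1 = 0.848 and MTX-alone rate p2 = 0.555; two-sided alpha 0.05 (u = 1.96); 90% power (u = 1.282); 50 per group before and 60 per group after the dropout allowance (all Sample size calculation). Two 4 g bags per day, placebo with 10% Juanbi pill (Interventions). Intention-to-treat with last observation carried forward (Statistical analysis).

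**Step 1: control exposure.** 2 × 4 g = 8 g per day of placebo. At 10%, that is 0.8 g per day of Juanbi pill against 8 g in the treated arm, a ratio of one-tenth. This assumes that 10% is by weight, which the article does not say.

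**Step 2: reproduce the stated sample size.** With p̄ = (0.848 + 0.555)/2 = 0.7015:

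- √(2 × 0.7015 × 0.2985) = 0.647
- √(0.848 × 0.152 + 0.555 × 0.445) = 0.613
- n = (1.96 × 0.647 + 1.282 × 0.613)² / 0.293² = 49.2, rounded up to 50 per group

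The numerator must be squared to get this; the printed formula omits the square and would give 23.9. The stated 50 is therefore right for an MTX-alone control, with power 90.5% at 50 per group.

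**Step 3: allow for the 10% content.** Let f be the share of the full 29.3-point effect that the 10% content delivers. The documents give no value for f, so it is an assumption and is shown as a range. The control rate becomes pc = 0.555 + f × 0.293, and with p̄ now the mean of p1 and pc:

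power = Φ{ [ (p1 − pc)√n − 1.96 √(2p̄(1 − p̄)) ] / √(p1(1 − p1) + pc(1 − pc)) }

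For f = 0.10: pc = 0.555 + 0.0293 = 0.5843 and the difference is 0.2637. At n = 50 this gives (1.865 − 1.250)/0.610 = 1.01, power 84.3%. At n = 60 it gives (2.043 − 1.250)/0.610 = 1.30, power 90.3%.

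| f (assumed) | Control rate | Difference (points) | Power, 50 per arm | Power, 60 per arm | Analysed per arm for 90% |
|---|---|---|---|---|---|
| 0 | 55.5% | 29.3 | 90.5% | 94.9% | 50 |
| 0.10 | 58.4% | 26.4 | 84.3% | 90.3% | 60 |
| 0.20 | 61.4% | 23.4 | 76.0% | 83.4% | 74 |
| 0.30 | 64.3% | 20.5 | 65.7% | 73.8% | 93 |

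The 50 column is the plan's own evaluable number. The 60 column is the number randomised, which the stated intention-to-treat analysis would use. It assumes that carried-forward outcomes show the same response rates as observed ones.

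**The case against.** A reader might infer that the trial is underpowered, or that 90% power is not delivered. The documents do not support that. It would need the ACR50 effect of the 10% content, which they do not give. If the content is inert, nothing is lost. Even with an effect proportional to amount, power is 90.3% when all 60 per arm are analysed. Power falls clearly below 90% at both sample sizes only if a tenth of the amount gives well over a tenth of the effect, and nothing in the article points to that.

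There is also a plausible reason for the 10% content. The same sentence says that the placebo resembles the real pill in appearance, smell and taste, which serves blinding. And if the effect does not fall as the amount rises, the dilution is conservative for efficacy: a positive result against this control would also support superiority over MTX without Juanbi. Only a null result becomes ambiguous. Finally, the Study design section describes a placebo-controlled trial of whether Juanbi plus MTX is effective. The phrase about MTX alone is a Discussion statement of the question.

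All of this stands, and it limits the power and safety points to conditional ones. A reader might also infer that the adverse-event comparison definitely understates the pill's risk; that too holds only if the 10% content causes events. None of it makes the control MTX alone. The blinding rationale explains the choice of product but does not correct the stated question or the source of the control rate.

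**Conclusion.** The mismatch in the contrast holds on the article's own text and needs no assumption about effect: the control contains the test product, so the trial does not directly estimate a difference from MTX alone. Only the figure of about one-tenth of the amount assumes 10% by weight.

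The power point holds in a limited form. The 90% is correct for the MTX-alone control of the preliminary experiment and is not shown for the control actually used. Over f from 0 to 0.30, power runs from 90.5% down to 65.7% at 50 per arm and from 94.9% down to 73.8% at 60. This range illustrates sensitivity to an unknown f. It is not an estimate, and 84.3% should not replace the stated figure. The possible upward shift in control response from blinding is a further uncertainty that the documents give no means to quantify.

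The correction matters because it changes what the trial can conclude, and the article intends its results to inform clinical decisions and guidelines.

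**What to change.** Reconcile Interventions, Sample size calculation and Discussion:

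1. Describe the comparator as MTX plus a control product containing 10% Juanbi pill. State the question as full versus 10% content on MTX, and remove the comparison with MTX alone from the intended conclusion. Alternatively, justify the 10% content as inactive.
2. Beside the sample size, state that the 55.5% comes from an open MTX-alone arm and that 90% power assumes the 10% content has no effect. Give the sensitivity range at both 50 and 60 analysed per arm, with f labelled as an assumption.
3. Report adverse-event rates for each arm, and note that controls are also exposed to the herbs when between-arm differences are interpreted.

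The cost is wording and a less favourable power statement. No change of product or patient numbers is proposed. Rewording does not restore power if the 10% content is active; it makes that dependence visible.

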### Randomization and allocation

Randomization will be conducted by a credible pharmaceutical manufacturer (Jiangyin Tianjiang Pharmaceutical Co., Ltd), which will provide both the Juanbi pill and the placebo. A random number list will be generated using Excel (Office 2016, Microsoft Corporation) to randomize participants either to the Juanbi pill group or the placebo group in a 1:1 ratio. When a participant is recruited, the investigator will provide the pharmaceutical manufacturer with a number, and the pharmaceutical manufacturer will randomly post the Juanbi pill or the placebo to the participant according to the random number list. The number provided and the corresponding number list will be recorded and will be kept in a locked cabinet at the pharmaceutical company.

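### The plan commits to 20:20 in each of three centres, but the single randomization list it describes has no stated feature that secures that balance

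*Protocol article*

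**What the plan says.** The Randomization and allocation section of the protocol article describes one list: "A random number list will be generated using Excel (Office 2016, Microsoft Corporation) to randomize participants either to the Juanbi pill group" or to placebo, in a 1:1 ratio. For each recruit the investigator sends the manufacturer a number, and the manufacturer dispatches active or placebo treatment according to the list. Blocking, fixed arm totals and stratification by centre are not mentioned.

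Other sections state exact numbers:

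- Study design: "In total, 120 patients with active RA will be recruited (60 patients per arm"), from three named hospitals.
- Sample size calculation: "a total of 120 patients (60 in each group), considering a 20% dropout rate".
- Sample size calculation, last sentence: "Forty participants (20 in the treatment group and 20 in the placebo group) from the three centers will be recruited".

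Taken literally, the last sentence gives 40 patients in all, which conflicts with 120. It agrees only if it means 40 from each centre, 20 per arm.

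The Quality control section makes the company responsible for randomization and also for allocation to the centres, without saying how. It also has monthly checks that each centre meets its recruitment number, but mentions no check of arm balance within a centre. The Statistical analysis section names Student's t test or a non-parametric test for continuous outcomes, and no centre term.

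**The concern.** The plan states an arm-by-centre split as a design fact, but the procedure it describes contains nothing that would produce it. This differs from leaving out a block size, which an article may properly do. Whether the list is stratified by centre decides whether the 20:20 sentence can be true other than by luck.

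ACR50 and DAS28 rest partly on joint counts made at three hospitals, so response levels may differ between centres. If the arms are unevenly spread over centres and the comparison ignores centre, part of the observed treatment difference in a given trial reflects centre. In a trial of 120 this adds noise and makes the result harder to defend. If exactly 20:20 is later reported, a reader will want to know how it was reached.

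**Working it through.** **1. The plan's own figure.** Inputs from the Sample size calculation section: "patients taking the Juanbi pill combined with MTX achieved 84.8% ACR50" and "patients in the MTX group achieved 55.5% ACR50 response", so p1 = 0.848 and p2 = 0.555; "a (two-sided) 5% significance level in detecting treatment differences", so u = 1.96; 90% power, so u = 1.282. The mean rate is (0.848 + 0.555)/2 = 0.7015.

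n = [1.96 × √(2 × 0.7015 × 0.2985) + 1.282 × √(0.848 × 0.152 + 0.555 × 0.445)]² / (0.848 − 0.555)²
= [1.268 + 0.786]² / 0.0858 = 49.2, or 50 per group.

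This reproduces the statement that "approximately 50 participants per group were needed to achieve 90% power". (The numerator must be squared; the square is missing in the printed formula.) The step to 60 is 50 × 1.2. By centre, 3 × 40 = 120 and 3 × 20 = 60 per arm, so the 20:20 sentence matches the totals only when read per centre.

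**2. Chance of the stated split without stratification.** The document does not say how the list is built, so two forms of a single list are compared. Both assume that each centre enrols exactly 40.

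(a) Coin-flip list, each entry independent at 1/2:
- 60:60 overall: C(120,60)/2^120 = 7.3%
- 20:20 in a given centre: C(40,20)/2^40 = 12.5%
- 20:20 in all three: 0.1254³ = 0.20%
- 25:15 or worse in a given centre: 15.4%; in at least one of three: 1 − (1 − 0.154)³ = 39%

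(b) One list fixed at 60/60 overall, not stratified by centre:
- 60:60 overall: 100%
- 20:20 in a given centre: C(40,20) × C(80,40)/C(120,60) = 15.3%
- 20:20 in all three: C(40,20)³/C(120,60) = 2.7%
- 25:15 or worse in at least one centre (exact sum over all splits): 19%

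(c) A separate list per centre fixed at 20/20 gives both 20:20 per centre and 60:60 overall with certainty, if each centre enrols exactly 40.

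**3. Consequence for inference.**

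| Patients | Split | Power |
|---|---|---|
| 120 | 60:60 | 94.9% |
| 120 | 52:68 | about 94.6% |
| 120 | 50:70 | about 94.3% |
| 100 completers | 50:50 | 90.5% |
| 100 completers | 42:58 | 89.5% |

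For the centre effect, an illustration assumes no treatment effect and response rates of 35%, 55.5% and 76% in the three centres. These spread-out rates are an assumption and are not in the document. With a coin-flip list and 100,000 simulated trials, the type I error is 5.1% and the mean treatment difference about 0. The part of the difference due to centre imbalance has a standard deviation of 3.1 percentage points and exceeds 5 points in about 9% of trials.

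**The case against.** The strongest objection is that the article never says the list is unrestricted, so a reader who concludes that it cannot deliver 60:60 or 20:20 goes beyond the text. This is correct. Sixty labels of each kind sorted by an Excel random number give 60:60 with certainty, and the same done with 20 and 20 for each centre gives 20:20. The company's role in allocating to centres, and the 20:20 sentence itself, may mean that allocation by centre was intended. An article may also leave block details to a fuller document. For this reason the point is that the balance is not secured as described, and the probabilities are given as a range over two forms of list.

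A reader might also infer that treatment is confounded with centre. The document does not support that. Chance imbalance under valid randomization leaves the estimate unbiased over repeated randomizations, and the illustration shows a type I error near 5%. Loss of power from unequal arms is below 1 percentage point for splits up to 50:70.

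Nor does it follow that filling centre quotas late would make allocations predictable in a harmful way. The manufacturer holds the list under any scheme, and the Blinding section says that its staff take no part in the trial and that those who enrol and assess patients are blinded.

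Finally, centre terms are often left to an analysis plan, and the t test does not apply to ACR50, which is binary. Both remarks are fair. They do not remove the mismatch between the 20:20 statement and the described list.

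**Conclusion.** The point holds in limited form. The article commits to 60 per arm and, read with the total of 120, to 20:20 in each centre, but describes only one 1:1 list with no stated restriction or stratification. On either form of a single unstratified list, the stated split would fail in more than 97% of trials (100% − 2.7% = 97.3% at best). At least one centre at 25:15 or worse would be common, at 19% to 39%. These figures assume 40 patients per centre and a list that ignores centre. They do not apply if the list was in fact built by centre, which the article leaves open.

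The cost is some precision and face validity, not validity of the test. It is worth correcting because the remedy is cheap and an analysis by centre is useful whether or not 20:20 was enforced.

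**What to change.** Reconcile the Study design, Randomization and allocation, Sample size calculation and Quality control sections, and make clear that the 40 patients are per centre if that is meant.

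- If the list is already restricted to 20:20 by centre, say so in one sentence. Block sizes need not be published.
- If it is not, allocate the remaining patients from permuted blocks of randomly varying size (for example 4 and 6), stratified by centre, with list and seed archived before use. Keep all allocations already made and delete the 20:20 statement.

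In either case, replace the comparison without centre by an analysis that includes it: Cochran-Mantel-Haenszel or logistic regression with centre for ACR50, and a linear model with centre and the baseline value for DAS28 and the modified Sharp score.

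**Cost.** If the list is already stratified, the cost is a sentence of text and slightly more analysis work. If not, the manufacturer must issue a new list in a blinded trial that has recruited since December 2016. That calls for a documented amendment and does not undo imbalance already present, which the analysis by centre then has to address.
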